### Sample size

The sample size is calculated for the investigation of the primary outcome, i.e., the prevalence rate of bacteriologically confirmed TB, that will be collected in Year 3. We estimated that the TB prevalence rate among the high-risk populations in the trial area is about 300 per 100,000 based on the TB prevalence survey conducted in 2010 in Guangxi [16]. We assume our intervention will reduce the rate among the high-risk populations in the intervention group by 50% (i.e., to 150 per 100,000) within 24 months, which can be considered as a significant reduction at the population level from public health perspective. We estimate that the intra-class correlation coefficient for TB prevalence was 0.001 [7]. The average number of eligible participants is about 500 per village based on household registrations. We estimate that we would need 47 villages (i.e., approximately 23,500 participants) in each group to have 80% power to detect the reduction estimated above, assuming p <  0.05.

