### Eligibility criteria

#### Clusters.

Township is treated as the cluster of intervention. A township is an administrative unit with a township hospital and consists of 7–12 villages. All townships in Xincheng and Xiangzhou county, which provide their willingness to participate, will be included. Villages within the participating township serve as sampling units in the epidemiological survey at Year 3 to determine the TB prevalence rate.

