### Recruitment, randomization and blinding

There are 23 townships and 255 villages in Xincheng and Xiangzhou county of Laibin city [17]. We will implement the ACF activities at the township level to avoid contamination among villages because township hospitals manage village doctors. We seek to recruit all townships of the two counties. After recruitment, the study statistician will use a custom-written computer program to randomize all recruited townships, stratified by county, assigning them to the control and intervention group in an overall 1:1 ratio (12 intervention vs 11 control) [18]. Then township/village doctors and county hospital staff in the intervention group will be invited to receive training about specific interventions in this project. After randomization is done at the township level, the statistician will then randomly select 47 villages, stratified by county, from each group for the Year 3 prevalence survey. The selection of villages for prevalence survey will be sealed and blinded to providers and investigators until the Year 3 prevalence survey to prevent any provider-related bias. We will seek written informed consent from each participant before enrollment, as we need to collect their health information, bio-sample (sputum) and test result for research purpose.

Due to the nature of the intervention, neither single nor double blindness procedure of the allocation of groups is applicable. However, we will blind the data analysts who process the end-point data for outcome assessment.

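### The stated 80% power treats villages as independent clusters, but townships are randomised, so power is below 80% for any positive township correlation

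*Protocol article*

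**What the plan says.** The Sample size section sizes the trial on the primary outcome: "The sample size is calculated for the investigation of the primary outcome, i.e., the prevalence rate of bacteriologically confirmed TB". Its inputs are:

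- control prevalence: "the TB prevalence rate among the high-risk populations in the trial area is about 300 per 100,000"
- effect: a reduction "by 50% (i.e., to 150 per 100,000) within 24 months"
- correlation: "We estimate that the intra-class correlation coefficient for TB prevalence was 0.001", with no statement of whether this is between people of one village or of one township
- cluster size: "The average number of eligible participants is about 500 per village based on household registrations"

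The result is "We estimate that we would need 47 villages (i.e., approximately 23,500 participants) in each group to have 80% power". That section does not mention the number of townships, the number surveyed per township, or a township-level correlation.

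The other sections use a different unit. Eligibility criteria, Clusters: "Township is treated as the cluster of intervention"; villages are described there only as sampling units for the Year 3 survey. Recruitment, randomization and blinding: the 23 townships are allocated, stratified by county, "in an overall 1:1 ratio (12 intervention vs 11 control"; the 47 villages per group are drawn only after that. Outcomes and Statistical analysis: village counts are aggregated to the township, and the primary model is a beta-binomial regression on township-level data.

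**The concern.** The sizing is done on 94 villages as if each had been allocated by itself. The design has 23 allocated units, each holding about 94/23 = 4.1 surveyed villages. Whatever makes villages of one township alike adds to the variance of the group comparison, and the calculation has no term for it. The protocol gives a reason to expect some likeness: it randomises townships because the township hospital manages the village doctors, so villages of one township share management and delivery of the intervention.

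At stake is how a null result is read. Statistical analysis makes the cluster-level estimates the primary evidence on effectiveness. A reader who trusts 80% power would take a non-significant result as fair evidence against a halving of prevalence, when the design may have had a much larger chance of missing it.

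**Working it through.** **Inputs.** From Sample size: p1 = 0.003, p2 = 0.0015, ICC 0.001, 500 per village, 47 villages per group, 80% power, alpha 0.05 (two-sided reproduces the figure). From Recruitment, randomization and blinding: 23 townships, 12 and 11. Assumed here, because the document gives none: the township ICC, meaning the correlation between people in different villages of one township. The village ICC (people in the same village) is held at 0.001.

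**1. The protocol's own figure.** Per group without clustering:

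n = (1.96 + 0.8416)² × (0.003 × 0.997 + 0.0015 × 0.9985) / 0.0015² = 15,659.

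Village design effect: 1 + (500 − 1) × 0.001 = 1.499. Then 15,659 × 1.499 = 23,472, and 23,472 / 500 = 46.9, so 47 villages. The published number is reproduced with the village as the cluster and no township term.

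**2. The same sample with townships added.**

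Design effect = 1 + 499 × 0.001 + (94/23 − 1) × 500 × township ICC.

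Effective n = 23,500 / design effect. Standardised difference d = 0.0015 / √[(0.003 × 0.997 + 0.0015 × 0.9985) / effective n]. Power is Φ(d − 1.96) with a normal reference, or from a noncentral t with 23 − 2 = 21 degrees of freedom.

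| Township ICC | Design effect | d | Power, normal | Power, t (21 df) |
|---|---|---|---|---|
| 0 | 1.50 | 2.80 | 80% | 76% |
| 0.0001 | 1.65 | 2.67 | 76% | 72% |
| 0.00025 | 1.88 | 2.50 | 71% | 66% |
| 0.0005 | 2.27 | 2.28 | 62–63% | 58% |
| 0.001 | 3.04 | 1.97 | 50% | 47% |

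(At 0.0005 the normal figure is 62% or 63% depending on whether the variance is pooled.) The last row applies the stated ICC in full to the declared cluster. With the exact 12 and 11 townships (design effects 2.96 and 3.14) it becomes 50–51% (normal) or 46% (t).

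A simulation of the beta-binomial model (1,600 runs, 23 townships of 4 villages, t reference) gave 66% at township ICC 0.0005 and 51% at 0.001. These are somewhat above the formula and still well below 80%.

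**3. Detectable effect.** Holding the control prevalence at 0.003 and solving for the prevalence ratio that gives 80% power (t, 21 df): about 0.48, 0.38 and 0.30 at township ICC 0, 0.0005 and 0.001. The protocol plans on 0.50.

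**4. Could more villages restore 80%?** There are only 23 townships, so extra villages fall inside the same townships and the design effect grows.

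- At township ICC 0.0005, 123 villages per group give a design effect of 1.499 + (246/23 − 1) × 0.25 = 3.92 and an effective n of 61,500 / 3.92, about 15,680. That just exceeds 15,659 (normal reference), but uses 246 of the 255 villages.
- At 0.001, the effective n per group cannot exceed 11.5 / 0.001 = 11,500 however many people are surveyed. This is short of 15,659, so 80% is out of reach.

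**The case against.** Five points can be made for the protocol.

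- **The township ICC is not in the document.** This stands. Every figure below the zero-correlation row is conditional. The lowest row is a limiting case in which villages add no clustering of their own. At a prevalence of 0.003, an ICC of 0.001 means a between-township coefficient of variation of √(0.001 × 0.997 / 0.003) = 0.58, which is large. If that coefficient, rather than the ICC, is held constant across groups, with total village-level variation kept, power is 78% (normal) or 74% (t) at 0.2, 73% or 69% at 0.3, and 54% or 51% at 0.58. Stratification by county may also remove some between-township variance.
- **The t reference is a reviewer's choice.** This stands in part: small-sample details can wait for the analysis plan. The main point does not need it, because the normal column also falls below 80% once the township ICC is above zero.
- **Participation.** A reader might infer that non-participation lowers power further. Residence is already part of eligibility, and the numerator also takes in cases reported by the National TB Program. The document gives no participation rate. With an assumed 400 surveyed per village (80%), t-based power would be 70%, 54% and 44% at township ICC 0, 0.0005 and 0.001. That is a sensitivity assumption only.
- **Inference is not invalid.** This stands. The primary analysis is at the level of randomisation and allows overdispersion between townships, and odds ratios with 95% confidence intervals are planned. The error is in the planning figure.
- **More villages would solve it.** One might scale 47 by the ratio of design effects: 47 × 2.27 / 1.499 = 71, or 47 × 3.04 / 1.499 = 95. This is wrong because it keeps 4.1 villages per township. With 23 townships fixed, 71 villages per group give only about 71% at township ICC 0.0005, and 95 give about 58% at 0.001 (normal reference).

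**Conclusion.** The concern holds. The 80% belongs to a trial that randomises villages, and this trial randomises townships. With the village ICC at 0.001, power for a 50% reduction is below 80% for any positive township correlation. It is about 46–51% if the stated ICC applies in full to townships, and rises to 76–80% only if township correlation is negligible. A reader might infer that the trial simply has about even odds of detecting a halving. The document does not support that as a single figure, because it states neither the level of its ICC nor a township component. The calculation assumes equal numbers surveyed per township within each group; villages are drawn with stratification by county only, and unequal numbers would lower power further.

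**What to change.** Rewrite the Sample size paragraph with the township as the cluster:

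- State 12 and 11 townships, about 4.1 surveyed villages each, separate and justified township and village ICCs, and a small-sample reference.
- Replace the 80% by the resulting power as a range over township ICC, such as the table above.
- Give the detectable prevalence ratio at 80% power (about 0.48, 0.38 and 0.30 at township ICC 0, 0.0005 and 0.001, t-based).
- State that a non-significant result does not by itself exclude a 50% reduction and that the confidence interval should be read for this.
- Show incomplete participation, if at all, as a labelled sensitivity assumption.

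No extra villages or participants are proposed, and conduct does not change. The cost is wording, and a stated figure that becomes less favourable.

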### Recruitment, randomization and blinding

There are 23 townships and 255 villages in Xincheng and Xiangzhou county of Laibin city [17]. We will implement the ACF activities at the township level to avoid contamination among villages because township hospitals manage village doctors. We seek to recruit all townships of the two counties. After recruitment, the study statistician will use a custom-written computer program to randomize all recruited townships, stratified by county, assigning them to the control and intervention group in an overall 1:1 ratio (12 intervention vs 11 control) [18]. Then township/village doctors and county hospital staff in the intervention group will be invited to receive training about specific interventions in this project. After randomization is done at the township level, the statistician will then randomly select 47 villages, stratified by county, from each group for the Year 3 prevalence survey. The selection of villages for prevalence survey will be sealed and blinded to providers and investigators until the Year 3 prevalence survey to prevent any provider-related bias. We will seek written informed consent from each participant before enrollment, as we need to collect their health information, bio-sample (sputum) and test result for research purpose.

Due to the nature of the intervention, neither single nor double blindness procedure of the allocation of groups is applicable. However, we will blind the data analysts who process the end-point data for outcome assessment.

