#### Research activities apply to both groups:.

We will wait for a year (cleaning period) to ensure all TB patients identified in Year 1 complete the treatment. Due to the constraint of resources, we can not conduct ACF activities covering all villages in Year 3. Instead, we will conduct an epidemiological prevalence survey in the intervention and control groups at Year 3 using cluster-random sampling methods at the village level, adopted from WHO [14,15], targeting high-risk populations in both intervention and control groups, to compare the TB prevalence rates. Regarding the survey, we will apply the same active case-finding activities as outlined above in both intervention and control groups.

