### Statistical analysis

The results of this project will be reported according to the ‘Consolidated Standards of Reporting Trials: Extension for Cluster Trials’ (CONSORT) guidelines [21]. We will report a detailed statistical analysis plan later. In the full research paper, we will present appropriate descriptive statistics for the two groups and all relevant baseline cluster and participant characteristics. We will aggregate information collected in Year 3 prevalence survey at the township level to calculate primary and secondary outcomes. In addition, using cluster-level methods of analysis, we can get a main set of estimates for our primary and secondary outcomes after the trial, acting as the primary evidence for determining the effectiveness of this trial. Appropriate summary statistics and their associated 95% confidence interval for all differences outcomes between the intervention group and the control group will be calculated. No interim analyses are involved in this project.

For the primary outcome and all secondary rate-based outcomes (aggregated to the township level), the statistical analysis will employ a beta-binomial regression model. The intervention effect will be expressed as an odds ratio with 95% confidence intervals. Secondary analyses will attempt to analyze the patient-level data adjusted for age, sex, and ethnicity using a mixed-effects logistic regression model including random effects for township and village (to reflect the sampling strategy). In the event of non-convergence of the two-level model, models where township is included as a fixed effect rather than random will be employed.

For continuous secondary outcomes we will employ a linear mixed-effect model with random effects for township and village. This model will also adjust for the following variables: age, sex, and ethnicity. In the event of non-convergence of the two-level model, models where township is included as a fixed effect rather than random will be employed. The intervention effect will be expressed as the adjusted mean difference with 95% confidence intervals.

We will conduct subgroup analyses by county to reflect if there is any different effect due to environmental factors in each county. If the secondary patient-level analyses can be successfully employed, a sub-group analysis by sex will be attempted.

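### Year 3 survey villages are drawn by county and arm but not by township, so a randomised township may have few or no surveyed villages; the cost is mainly a cluster at risk and a small loss of precision, not bias

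*Protocol article*

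**What the plan says.** The eligibility section makes the township the cluster and adds: "A township is an administrative unit with a township hospital and consists of 7–12 villages". Recruitment, randomization and blinding gives the frame, "There are 23 townships and 255 villages in Xincheng and Xiangzhou county of Laibin city", and the allocation, "assigning them to the control and intervention group in an overall 1:1 ratio (12 intervention vs 11 control".

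After randomisation, "the statistician will then randomly select 47 villages, stratified by county, from each group for the Year 3 prevalence survey". That list "will be sealed and blinded to providers and investigators until the Year 3 prevalence survey".

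Statistical analysis then returns to the township: "We will aggregate information collected in Year 3 prevalence survey at the township level to calculate primary and secondary outcomes". The primary model is a beta-binomial regression on these township aggregates.

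Two other sentences describe the sampling. The eligibility section says "Villages within the participating township serve as sampling units in the epidemiological survey at Year 3 to determine the TB prevalence rate", and the section on research activities in both groups describes "using cluster-random sampling methods at the village level, adopted from WHO". Both name the village as the sampling unit. Neither sets a quota or minimum per township, and nothing says what happens to a township in which no village is drawn.

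**The concern.** The outcome sample is stratified by a unit (county) that is not the unit of analysis. Within a county and arm, all villages form one pool, so a township can receive seven survey villages or none.

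A township with none was randomised but has no survey data for the primary comparison. A township with one rests on about 500 people, which at the planning rates means about 1.5 expected cases in control (500 × 0.003) and 0.75 under intervention (500 × 0.0015). With only 23 townships, and roughly five or six per arm in each county for the planned county subgroups, each township counts. Uneven numbers of villages also cost some precision between townships.

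**Working it through.** **Inputs from the protocol.** 23 townships and 255 villages (mean 255/23 = 11.1); 12 against 11 townships; 7–12 villages per township; 47 villages per arm; about 500 eligible people per village; prevalence 300 against 150 per 100,000; ICC 0.001.

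**Assumptions.** The county split is not given. I took 6 and 6 intervention townships and 6 and 5 control townships. Villages per arm are then about 133 and 122 (the 7–12 pattern below gives 134 and 121). Each county's share of the 47 is proportional to its villages.

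**The plan's own figure.** Two proportions, two-sided 5%, 80% power: 15,662 per arm. Design effect 1 + (500 − 1) × 0.001 = 1.499. Product 23,477, or 46.95 villages, so 47. The stated sample size reproduces, with the village as the cluster.

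**Chance that one township is missed.** With N villages in a county-arm pool, k drawn and s in the township, P(none) = C(N − s, k)/C(N, k).

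- 11-village township, intervention, N = 66, k = 24: 0.40%; none or one, 3.7%.
- 11-village township, control, N = 66, k = 26: 0.22%; none or one, 2.3%.
- 7-village township, intervention, N = 62, k = 22: 3.8%; none or one, 21%.

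If every township has 11 villages, summing over all 23 gives 0.08 expected empty townships and 0.76 with none or one.

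**Chance over all 23 townships** (multivariate hypergeometric simulation, 100,000 draws):

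| Township sizes assumed | At least one empty | At least one with 0–1 village |
|---|---|---|
| All 11 | 8% | 56% |
| Within 7–12 (four of 7, one of 11, the rest 12) | 17% | 75% |
| Wider, 7–16 | 19% | 79% |

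The last row exceeds the stated 7–12 range and serves as a stress case.

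**Precision.** A beta-binomial model weights a township of m people approximately by m/(1 + (m − 1) × ICC). At ICC 0.001 this gives an effective 334 people for one village (m = 500), 500 for two, 667 for four and 714 for five. Information flattens as villages are added, so villages that fall by chance in a well-covered township recover only part of what a thin township loses.

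I summed these weights per arm for the county-only draw and for a draw allocated in proportion to township size (60,000 simulated draws):

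| Sizes | Information kept, intervention / control | Power, proportional → county-only |
|---|---|---|
| All 11 | 96.4% / 97.2% | 50.6% → 49.3% |
| Within 7–12 | 95.8% / 96.5% | 50.4% → 48.9% |
| 7–16 | 96.7% / 96.9% | 49.9% → 48.6% |

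The loss is about 3% (2.8–4.2% across arms and patterns), or 1.3–1.6 power points. Empty townships are included.

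**The case against.** **Detail may lie elsewhere.** The article condenses a fuller proposal, cites WHO survey methods and defers a statistical analysis plan, so a township allocation rule may exist. That possibility stands, but the article states a specific rule with county as its only stratum. If the full document differs, the article needs one correcting sentence.

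**The remedy may be too late.** Study status and timeline gives a start in November 2021, a three-month suspension and completion of data collection by the end of January 2025. Thirty-six months plus three puts Year 3 at roughly February 2024 to January 2025, so the list may already have been open at submission. This is an inference, since the submission date is not shown. It limits the remedy without removing the mismatch.

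**A reader might infer a larger loss of precision.** The usual formula for unequal clusters, 1 + ((1 + cv²)m − 1) × ICC with m = 2,043 and cv² of 0.12–0.16, moves the design effect from 3.04 to 3.29–3.37, a rise of 8–11%. That formula suits an estimator weighting townships by raw sample size and compares with perfectly equal townships. The stated model weights approximately by information, and a proportional draw from townships of 7–12 villages is itself somewhat unequal. About 3% is the fairer figure.

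**A reader might infer bias.** The documents do not support that. The draw is random, the list is concealed from providers and investigators, the model uses denominators, and a township is missed only by the luck of the draw.

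**The starting power near 50% is a separate matter.** It arises from applying the ICC at township level, whereas the sample size applies it at village level. It should not be counted against the village draw.

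**Conclusion.** The point holds as a mismatch between the sampling rule and the unit of analysis, with modest consequences. A wholly empty township is unlikely (about 8–19% for at least one; 8–17% if sizes stay within 7–12). At least one township with none or a single surveyed village is more likely than not (about 56–79%). The possible loss of a randomised cluster matters more than the precision cost of about 3%.

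The probabilities rest on an assumed near-even county split and assumed township sizes. The power figures also require ICC 0.001 between townships. If clustering exists only between villages, the count of 47 per arm is unaffected and the precision loss largely disappears, but the risk of an empty or near-empty township remains.

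**What to change.** **If the sealed list has not been opened:** stratify the draw by township within county and arm, keeping 47 villages per arm and allocating them in proportion to each township's number of villages. Require at least one, preferably two, per township. A 7-village township then receives 2–3 (7 × 47/133 = 2.5; 7 × 47/122 = 2.7) and a 12-village township 4–5 (12 × 47/133 = 4.2; 12 × 47/122 = 4.6). Village selection chances stay nearly equal, so the sample remains close to self-weighting.

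A flat four per township would not be proportional: it takes 4/7 = 57% of the smallest townships and 4/12 = 33% of the largest, and would need weights.

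The cost is one sentence in the protocol and a new random draw. The 94 villages and the survey volume are unchanged.

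**If the list has been opened:** keep the existing draw. Report villages and people surveyed in each township, and state before unblinded analysis how a township with no survey data is treated in the primary model. This costs a table and a sentence.

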#### Intervention.

In the intervention group, in addition to usual care, we will implement an ACF campaign among all eligible participants in Year 1 (Fig 3). Prior to the visit, village social workers and village doctors will conduct door-to-door visits to recruit participants and obtain their informed consent. We will drive the mobile van to the village, and equip an AI-facilitated digital radiography (DR) machine and refrigerator on the van on a mutually agreed date. On the day, all eligible participants will be invited to complete a brief questionnaire regarding basic demographic information, medical history, smoking status and TB related symptoms, and then are invited to have their DR examined in the van. Based on digital chest X-rays, the AI software will identify TB assumptive participants who may have active TB, suspected TB or healed TB. In the first month of implementation in each county, one township hospital radiologist will facilitate the X-ray examination, double-check all results of the AI software, and make the final recommendation for presumptive TB. This process will be recorded to adjust the threshold score used by AI in each county. After the first month, the township hospital radiologist will still accompany the mobile clinic to help evaluate X-ray results if AI suggests for other lung diseases such as pneumonia or lung cancer, to minimize the risk of missing possible TB cases. Those who are presumptive of TB based on either DR examination or TB-related symptoms, i.e., any chronic cough over two weeks, hemoptysis, fever, night sweats, chest pain or unexplained weight loss, will be asked to produce a single on-site sputum. These villagers are also asked to take two specimen boxes for the collection of night and morning sputum. All staff are trained for good quality sputum sample collection, storage and transportation. Medical nebulizer inhalation will be provided to those who can not provide good-quality sputum. Sputum samples, either collected on the day or delivered by village doctors within 48 hours, will be stored in the refrigerator on the mobile van and transported back to the County Hospital daily for sputum testings, including smear microscopy, culture and GeneXpert assay. We will employ a sample mixing approach which has been validated in our previous publication [13]. Bacteriologically confirmed TB is defined by a positive result from any of the above sputum tests based on WHO and China National TB Program guidelines. Participants who are bacteriologically negative but have abnormal X-ray result or TB symptoms are referred to the county hospital for clinical assessment by a panel committee consisting of three senior doctors based on China National TB guideline for the diagnosis of clinically confirmed TB. All diagnosed TB patients, either bacteriologically or clinically confirmed, will be notified by the village doctor within 48 hours and referred to the County Hospital for standard WHO DOTS regimens per national guidelines.

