#### Laboratory testing and clinical consultation.

The county hospitals will carry out laboratory testing according to the ‘TB Laboratory Testing Protocol’. Sputum smear test, GeneXpert test and sputum culture are carried out at the same time. Every five samples of sputum will be mixed for GeneXpert test to save costs. Mixed samples that are positive will be re-tested individually to confirm the positive case. Country hospitals will distribute the laboratory testing results to patients within 48 hours. All TB diagnoses will be recorded in the ‘Register of Newly Diagnosed Patients’ in the National TB Program Registry. Clinical diagnosis based on the clinical assessment will be performed by a group of senior doctors in county hospitals according to the National TB Classification Criteria (WS196–2017) and Diagnostic Criteria (WS288–2017) [19,20]. We will collect TB cases diagnosed and reported in the National TB Program in both intervention and control groups through the three years.

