#### Determination of the primary and secondary outcomes.

We will combine the TB cases identified from the Year 3 prevalence survey and TB cases reported from the National TB Program to determine the numerators of our outcomes. The data collection approach in Year 3 for the outcome evaluation will be the same as the ACF activities conducted in the intervention group in Year 1. We will use the TB diagnosis algorithm as defined in our ACF to determine the bacteriologically confirmed and clinically confirmed cases. We will also collect the routinely reported TB cases through the National TB Program for Year 3. We will collect the information of all registered permanent residents who reside in the village at the time of Year 3 survey to determine the relevant denominators.

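### The protocol calls blinding inapplicable and masks only the data analysts, although the county laboratory staff who read Year 3 sputum could be masked to arm with coded specimens.

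*Protocol article*

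**What the plan says.** Under Recruitment, randomization and blinding, the protocol article says "Due to the nature of the intervention, neither single nor double blindness procedure of the allocation of groups is applicable". The next sentence gives the only masking to arm: "However, we will blind the data analysts who process the end-point data for outcome assessment". The same section describes one further concealment: "The selection of villages for prevalence survey will be sealed and blinded to providers and investigators until the Year 3 prevalence survey". That hides which villages will be sampled, not which arm they belong to, and it ends when outcome assessment begins.

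Randomization is by township, stratified by county (12 intervention, 11 control). After it, "Then township/village doctors and county hospital staff in the intervention group will be invited to receive training about specific interventions in this project".

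For the outcome survey, the section on determination of outcomes has data gathered by the method of the first-year campaign. The research activities section says that the same case finding is applied in both groups. Under Intervention, sputum "will be stored in the refrigerator on the mobile van and transported back to the County Hospital daily for sputum testings", and the laboratory section places this testing with the county hospitals under a written laboratory protocol. Smear, culture and GeneXpert are run at the same time, with GeneXpert on pools of five. Under Outcomes, a positive result on any one of the three tests makes a bacteriologically confirmed case, which is the primary outcome.

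**The concern.** The nature of the intervention explains why villagers, village doctors and the van team cannot be blinded. It does not explain why a microscopist at the county hospital must know which township a slide came from. The blinding sentence treats masking of participants and providers and masking of outcome assessors as one thing, and gives up both.

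Smear microscopy depends on the reader, particularly for scanty slides. A reader who knows the arm and knows what the trial hopes to show may read doubtful slides differently, without intending to. One such reading can create a primary-outcome case. Analyst blinding acts after case status has been fixed and cannot undo this. With low prevalence and few expected cases, the estimate is sensitive to a small number of readings.

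**Working it through.** **Step 1: can the laboratory be masked?** Three statements in the protocol article bear on this.
- Randomization is stratified by county, so each county contains both arms, and its county hospital receives Year 3 sputum from both.
- Year 3 uses the same procedures in both arms, so nothing in the laboratory work itself reveals the arm.
- Sputum leaves the village on the van and is tested at the county hospital, so the reader is separated from the participant.

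The reader could therefore work from a coded specimen. No section says that this is done.

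**Step 2: reproduce the plan's sample size.** Inputs from the Sample size section: 300 v 150 per 100,000, intra-class correlation 0.001, 500 eligible per village, 80% power, p < 0.05 (taken as two-sided).
- n per group = [1.960 × √(2 × 0.00225 × 0.99775) + 0.842 × √(0.003 × 0.997 + 0.0015 × 0.9985)]² / 0.0015² = 15,662
- Design effect = 1 + (500 − 1) × 0.001 = 1.499
- 15,662 × 1.499 = 23,477; 23,477 / 500 = 46.95, so 47 villages.

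This matches the stated 47 villages and approximately 23,500 participants per group. Nothing in it depends on blinding.

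**Step 3: expected cases.** Control: 23,500 × 0.003 = 70.5. Intervention: 23,500 × 0.0015 = 35.25. Planned ratio: 35.25 / 70.5 = 0.50.

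**Step 4: sensitivity to a few false-positive smears (assumed, not in the document).**
- Five extra in the control arm only: 35.25 / 75.5 = 0.47
- Five extra in the intervention arm only: 40.25 / 70.5 = 0.57

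**Step 5: effect on the false-positive rate of the trial (assumed).** Suppose there is no true effect, with 300 per 100,000 in both arms. Suppose further that 10% to 30% of participants give sputum, and that unmasked smear reading is 0.2 percentage points less specific in the control arm. Extra control cases are 23,500 × fraction tested × 0.002. The chance of a significant result favouring the intervention uses an effective size of 23,500 / 1.499 = 15,677 per group and a normal approximation.

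| Fraction giving sputum | Extra control cases | Apparent ratio | Chance of a false favourable result (nominal 2.5%) |
|---|---|---|---|
| 10% | 4.7 | 70.5 / 75.2 = 0.94 | 5.0% |
| 20% | 9.4 | 70.5 / 79.9 = 0.88 | 9.1% |
| 30% | 14.1 | 70.5 / 84.6 = 0.83 | 15.1% |

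This takes over the design effect of the sample size section. It is not a simulation of the planned township-level beta-binomial analysis.

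**The case against.** The strongest reply is that most of the outcome pathway leaves little room for a reader's judgement. GeneXpert and the AI score are largely automatic. Because the three tests run in parallel, under-reading a smear removes a case only if GeneXpert and culture are also negative. Routinely reported cases enter the primary numerator too, and no survey step can mask them. Data collection was under way at submission and due to end by January 2025, so little may be left to code. The training sentence does not name laboratory readers, so their knowledge of the arm is an inference.

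All of this stands and limits the point. The remaining route is mainly false-positive smear reading, which coding can address. Several stronger readings that a reader might infer do not stand:

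- **Coded samples would also mask X-ray review.** The radiologist is on the van in the village. After the first month in each county, the role is limited to films where the AI suggests another lung disease. Masking that step would need off-site reading.
- **Coded files would mask the clinical diagnosis.** Participants are referred for "clinical assessment by a panel committee consisting of three senior doctors" and can reveal where they live or that they were screened before. A later re-read by the same three doctors would not be masked either, since they have already decided the case.
- **The panel defines the cost-effectiveness result.** The Costing study section refers to active TB but says that it uses data from the primary outcome, which is bacteriological. The panel's role there is not established.
- **Masking is free of staff time.** The document gives no staffing or masking costs, and someone has to code and unlink specimens.
- **Readings shift by five in each arm in opposite directions.** That would give 30 / 75 = 0.40 or 40 / 65 = 0.62, but it requires losing cases in one arm, which the parallel tests make hard.

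**Conclusion.** The point holds for the laboratory readers of Year 3 survey sputum. The protocol declares blinding inapplicable without qualification, while its own design sends specimens from both arms to a laboratory away from the village under one algorithm. The primary outcome can turn on a single smear or culture, and masking the analysts comes too late to protect it.

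The exposure is moderate. Under the one-directional assumptions above, five extra false-positive smears in one arm move a planned ratio of 0.50 to 0.47 or 0.57. With no true effect, the chance of a false favourable result rises from 2.5% to between 5% and 15%. The shift in readings, its direction and the fraction giving sputum are all assumed. The document gives no evidence that biased reading has occurred. The planned 47 villages per group and 80% power are unaffected.

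**What to change.** 1. For the remaining Year 3 survey specimens, label sputum with a study code that hides village, township and arm from the smear, culture and GeneXpert readers. The link should be held by someone who reads no specimens.
2. Mix specimens from both arms within laboratory batches where daily transport and the 48-hour reporting of results allow. Where a day's van load comes from one arm only, record this, because the batch itself may then reveal the arm.
3. Replace the blanket sentence with one that names who is masked and what stays open, for example: laboratory readers of survey specimens and data analysts are masked to allocation; participants, field staff, on-van X-ray review, the in-person clinical panel and routinely reported cases are not. Claim laboratory masking only for specimens that were in fact coded.
4. For specimens already read openly, if smear slides have been retained, have them re-read under code by a reader who did not make the first reading. Report the primary outcome with the re-read results as a sensitivity check. The document does not say whether slides are kept.

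The cost is modest work to code and unlink specimens and to plan batches, plus reading time if step 4 is done. No participant procedure, sample size or primary analysis changes.
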